**Reported by investigator to sponsor**

The CI of the study will report the reportable events to the sponsor not later than 3 calendar days after investigational site study personnel’s awareness of the event.

**Reported by sponsor to MHRA**

Reportable events will be reported at the same time to the MHRA by the sponsor through the Yellow Card Scheme.

**Investigation**

The MHRA, the sponsor and the investigators of the study may investigate the problem depending on how serious it is.

**Causality assessment** The relationship between the use of the LiveOCT device and the occurrence of each adverse event shall be assessed and categorized. For the purpose of harmonising reports, each SAE will be classified according to five different levels of causality (MEDDEV 2.7/3 revision 3).
 • Not related
 • Unlikely
 • Possible
 • Probable
 • Causal relationship

The study will be halted immediately once any AE or SAE occurs.

Testing will be halted immediately if the participant becomes distressed or indicates that they wish testing to end, the authorised users will report the AE to the Chief Investigator ([name])

1. Financing and insurance

The study is fully funded by a NIHR i4i Product Development Award. The NIHR Clinical Research Network North West Coast (CRN-NW) and The LUHFT have jointly attributed all activities associated with the clinical study using the AcoRD model and provided the NHS Treatment Costs, Service Costs and Research Costs.

1. Peer review

Thorough peer review was carried out during application to the funder for this research and this protocol was peer reviewed by [name], consultant ophthalmologist at the Liverpool University Hospitals NHS Foundation Trust, and [name] at the University of Lincoln.

1. Audits

The study will be subject to inspection and audit by the sponsor (TBD) under their remit as the sponsor and other regulatory bodies to ensure adherence to GCP and the UK Policy Framework for Health and Social Care Research (v3.2 10th October 2017).

1. Dissemination and intellectual property

The dissemination activities of the study outcomes will be carefully planned to be compatible with the protection of IP. For the purposes of IP protection, during the project all publications, presentations, and other dissemination-related activities shall first be reviewed by [name] and the IP team within the University, and the funder i4i Programme Secretariats. The new IP generated will be protected under the agreement between The University of Liverpool and Liverpool University Hospitals NHS Foundation Trust.

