## Secondary outcomes

**Repeatability/reproducibility:** Outcome metrics will be the repeatability and reproducibility of measurements (identification and thickness) of structural parameters of the cornea, corneal surface contour and refractive power.

**Sensitivity and specificity:** We will use published grading systems specific to the two main conditions of FECD and keratoconus. For keratoconus, the sensitivity of the LiveOCT will be assessed by its ability to detect the same diagnostic parameters of non-uniform and focal corneal thinning and irregular and non-asymmetric anterior and posterior corneal profiles currently measured using the Pentacam. For FECD, the sensitivity of the LiveOCT will be assessed by its ability to measure increases in corneal thickness and areas of corneal swelling, and excrescences (guttata) and thickening of Descemet's membrane in patients who have guttata evident with slit lamp bio microscopy and increased corneal thickness measured with the Pentacam. Specificity will be defined as the percentage in which the described diagnostic changes in the cornea for keratoconus and FECD are not apparent with the LiveOCT device.

**Patient experience:** Study participants will be asked to fill in a simple set of questions concerning their experience with the LiveOCT devices. The patients will be asked to fill out paper copies of the questionnaire after the end of each study appointment, but the study nurse will be available to help if required.

If the participant indicates that they are feeling particularly anxious or depressed on the questionnaire, a member of their care team will pass this information onto their GP.

**Cost Effectiveness:** See 13.3 - economic evaluation

1. Definition of end of study

The study will be completed and terminated on 31st October 2022, which is defined to be the date when analysis of the data collected during the trial is being completed.

Suspension or early termination of the study when there are serious concerns about subjects’ safety and inadequate performance, that cannot be mitigated by modifications of the study protocol based upon the review of the safety data.

1. Discontinuation/ withdrawal of participants from study treatment

If a decision is made by the participant and or/clinician not to continue with the study, the participant will be removed from it and the event recorded. Data will still be collected unless the participant explicitly withdraws consent for it.

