## Archiving

Data collected, required software to read and associated analyses will be deposited in a data archive at the end of the project and stored for 15 years.

Frequent backups are performed using the best enterprise backup solutions at LUHFT as well as UoL, and are physically stored in a fire-proof safe. The backup strategy will be implemented to support hourly, daily, monthly and yearly retention.

1. Monitoring

Study monitoring will be carried out to ensure that the rights and well-being of the participants are protected during the study. A risk assessment will be performed prior to initiation. This will be completed in partnership with representatives of the study sponsor, the Chief Investigator, the Clinical Lead and the Study Manager.

The study will be managed by an Executive group, which will meet face-to-face 3 to 4 times per year and by teleconference approximately fortnightly. The Executive group for the study will be chaired by the Chief Investigator and will consist of the applicants and the trial manager.

The study will be overseen by a study steering committee that will be convened before the start of recruitment.

Membership of the study steering committee will include:

- Independent chair ( [name], Consultant Ophthalmologist at The Royal Liverpool University Hospital)
- Independent Patient representative ([name], ED Society)
- Independent Clinical Representative ([name], Consultant Ophthalmologist at The Royal Liverpool University Hospital)Study representative ([name], Chief Investigator) – non independent member

The steering committee will check that we are adhering to protocols and recording data and adverse events appropriately and accurately at month 3 and month 6 of the study.

1. Ethical and regulatory considerations

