## Approvals

## All approvals (NRES, MHRA Notice of No Objection and HRA) will be in place before we commence recruitment. Adverse event and safety reporting

*The research team do not expect there will be any AE or SAE, however, in the event they do occur, the procedures below will be followed.*

Definitions from the ‘Guidelines on Medical Devices’ from the European Commission (‘Clinical investigations: serious adverse event reporting under directives 90/385/EEC and 93/42/EEC’) and the examples that would apply to the LiveOCT study are presented in the table below

| **Term** | **Definition** | **Example(s) applying to LiveOCT.** |
| --- | --- | --- |
| Adverse Event (AE) | Any untoward medical occurrence, unintended disease or injury or any untoward clinical signs (including an abnormal laboratory finding) in subjects, users or other persons whether or not related to the investigational medical device.  NOTE 1: This definition includes events related to the investigational device or the comparator.  NOTE 2: This definition includes events related to the procedures involved.  NOTE 3: For users or other persons, this definition is restricted to events related to investigational medical devices. | Irritation of forehead chin/ hands in contact with device.  Irritation of eye from Laser  Trapping of fingers in device |
| Serious Adverse Event (SAE) | Adverse event that:  a) led to a death, injury or permanent impairment to a body structure or a body function.  b) led to a serious deterioration in health of the subject, that either resulted in:  - a life-threatening illness or injury, or  - a permanent impairment of a body structure or a body function, or  - in-patient hospitalization or prolongation of existing hospitalization, or  - in medical or surgical intervention to prevent life threatening illness  c) led to foetal distress, foetal death or a congenital abnormality or birth defect.  NOTE 1: Planned hospitalization for pre-existing condition, or a procedure required by the Clinical Investigation Plan, without a serious deterioration in health, is not considered a serious adverse event. | Serious electrocution  Serious injury of eye from laser |
| Device Deficiency | Inadequacy of an investigational medical device related to its identity, quality, durability, reliability, safety or performance. This may include malfunctions, use error, or inadequacy in the information supplied by the manufacturer. | Device presents misleading information |

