| Adverse Device Effect (ADE) | Adverse event related to the use of an investigational medical device.  NOTE 1: This includes any adverse event resulting from insufficiencies or inadequacies in the instructions for use, the deployment, the implantation, the installation, the operation, or any malfunction of the investigational medical device.  NOTE 2: This includes any event that is a result of a use error or intentional abnormal use of the investigational medical device. | As device deficiency  Patient face knocked with device whilst aligning. |
| Serious Adverse Device Effects (SADE) | Adverse device effect that has resulted in any of the consequences characteristic of a serious adverse event. | As SAE.  Device falls onto patient requiring hospitilisation |
| Unanticipated Serious Adverse Device Effect (USADE) | Serious adverse device effect which by its nature, incidence, severity or outcome has not been identified in the current version of the risk analysis report.  NOTE: Anticipated SADE (ASADE): an effect which by its nature, incidence, severity or outcome has been previously identified in the risk analysis report. | Photo induced epileptic seizure. |

The CI will investigate all adverse events and reactions and grade and record them in the patients CRF. Any patient who has an adverse reaction will be referred to either the Accident and Emergency Department or the St. Paul’s Primary Eye Care Department of the RLUH within LUHFT or to their General Practitioner depending on the situation. The monitoring of the reporting of adverse events and reactions will be undertaken by a study steering committee chaired by Consultant Ophthalmologist, Mr [name]

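### The study-level halt in section 16.2 is triggered by any adverse event, however minor or unrelated, names no one to lift it and no condition for restarting, and is not linked to section 11.

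*Protocol*

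**What the plan says.** **The halt.** Section 16.2 (Adverse event and safety reporting), under causality assessment, says: "The study will be halted immediately once any AE or SAE occurs". The sentence after it covers a different case: testing stops if the individual participant is distressed or asks to stop.

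**What counts as an AE.** The definitions table in section 16.2 includes events in subjects "whether or not related to the investigational medical device". Its examples for this device run from skin irritation at points of contact and a trapped finger to eye irritation from the laser.

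**Section 11 (Definition of end of study).** Suspension or early termination is tied to serious concerns "that cannot be mitigated by modifications of the study protocol based upon the review of the safety data". The same section fixes the end: "The study will be completed and terminated on 31st October 2022".

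**Other handling of AEs.**
- Section 16.2: "The CI will investigate all adverse events and reactions and grade and record them in the patients CRF".
- Section 16.2: the relationship between device use and "the occurrence of each adverse event shall be assessed and categorized". A five-level causality scale, including a level for no relation, is then set out for SAEs.
- Section 16.2: the MHRA, the sponsor and the investigators "may investigate the problem depending on how serious it is".
- Section 15 (Monitoring): the steering committee checks protocol adherence and "recording data and adverse events appropriately and accurately at month 3 and month 6 of the study".

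No section says who lifts a halt, on what evidence, or what happens to LiveOCT imaging that falls due during one.

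**The concern.** A halting rule has to say what triggers it, who reviews the event, and how the study resumes or ends. This one gives only the trigger, and that trigger has no lower limit. Seriousness is irrelevant because non-serious AEs are named. Relatedness is irrelevant because the AE definition includes unrelated events.

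This leaves staff with two poor choices. They can apply the sentence literally and stop recruitment and LiveOCT imaging for everyone after, say, an unrelated minor illness in one participant, with no stated way back. Or they can use common sense and carry on, which departs from the Protocol as written. Because the end date is fixed, time spent in a halt is taken from recruitment or from the 3- and 6-month imaging schedule.

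**Working it through.** The Protocol gives no AE rate and no halt length, so there is no figure of its own to reproduce. The check is mainly a comparison of texts, with some arithmetic for context.

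**1. Does the rule act on the study or on the participant?** The halt sentence has the study as its subject. The next sentence has testing as its subject and deals with one participant. Having separate sentences for the two supports a study-level reading of the first.

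**2. Is there a threshold?** The rule covers any AE or SAE. The AE definition covers related and unrelated events, and the examples include trivial ones. Causality is to be assessed and investigation may depend on seriousness, but neither feeds into the trigger. There is no threshold.

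**3. Is there an exit?** The Executive group and steering committee (section 15) and the sponsor (section 16.2) could each decide. None is given the decision, and no restart condition is stated.

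**4. Is the rule linked to section 11?** Section 11 covers suspension as well as termination, and sets its bar at serious concerns that remain after safety review and possible protocol changes. Section 16.2 halts at once for anything. Neither section mentions the other.

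**5. How much room does the calendar leave?** Section 1 gives a study period of 1 May 2021 to 30 October 2022, about 18 months. Each participant needs 6 months, so at most 18 − 6 = 12 months remain to enrol 90, an average of 90/12 = 7.5 per month. Twelve months is an upper bound, because section 11 places completion of the analysis at the end date too.

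**6. What would a halt stop?** Planned visits: 90 × 3 = 270. The section on baseline and subsequent assessments makes all keratoconus visits standard care, and all FECD visits except month 3. Treating the lamellar-surgery patients like FECD (an assumption):

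| Group | Standard-care visits | Research-only visits |
|---|---|---|
| Keratoconus (40) | 40 × 3 = 120 | 0 |
| FECD/lamellar surgery (30) | 30 × 2 = 60 | 30 × 1 = 30 |
| Healthy volunteers (20) | 0 | 20 × 3 = 60 |
| Total | 180 | 90 |

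So 180 of 270 visits could go ahead as clinical care. LiveOCT imaging, the only extra test, would be lost at any visit that falls within a halt.

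**7. How likely is a trigger? (Illustration only.)** With an assumed 6-month AE risk p per participant, independent events and no dropout, the chance of at least one AE among 90 is 1 − (1 − p)^90:
- p = 0.1%: 8.6%
- p = 1%: 59.5%
- p = 5%: 99.0%

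The range is wide because the Protocol gives nothing to narrow it.

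**The case against.** **A low threshold can be defended.** The device is newly moved from the laboratory to living eyes, it uses a laser, and participants may be as young as 12 or have a learning disability. This stands against a trigger limited to SAEs, which would drop the halt for non-serious laser-related eye irritation, where a device signal might first show. It does not justify halting for events unrelated to the device, or leaving out a restart rule.

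**A reader might infer that section 16.2 contradicts section 11.** The documents do not support that. An immediate precautionary halt could come first, then safety review, then the section 11 decision. The Protocol does not say that it works this way, and section 11 also speaks of suspension, so the fault is a missing link between two rules.

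**A reader might also infer, from the grading, causality assessment and committee checks, that the study was meant to continue after an AE.** That does not follow. All of these steps can be carried out during a halt, and the committee's checks would apply even if no AE occurred.

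**The intended scope may be narrower.** The listed examples all concern the device, and the next sentence treats a distressed participant's event as an AE handled by stopping that person's testing. A session-level or device-related trigger may have been meant. If so, the text needs to say it, because the sentence and the definition together do not.

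**The team expects no AE.** Section 16.2 says so, but adds that its procedures apply if one occurs, so the rule is meant to operate.

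**Conclusion.** The point holds as a badly fixed operational rule. Read literally, section 16.2 halts the whole study for any AE regardless of seriousness or relatedness, gives nobody the restart decision, states no restart condition, and is not tied to section 11. The conclusion rests on the study-level reading, which the wording favours.

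The consequence is a possible stop to recruitment and LiveOCT imaging within an enrolment window of at most 12 months. The size of any delay cannot be derived: halt length and AE rate are not in the Protocol, and the probabilities above only illustrate assumed risks. A reader might infer that every visit would stop, but 180 of the 270 planned visits belong to standard care and could continue without LiveOCT imaging. A reader might also infer damage to the analysis. No effect on bias, power or sample size is claimed. The matter is worth fixing because the correction is cheap and the present text cannot be followed sensibly.

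**What to change.** Replace the halt sentence in section 16.2 with a rule along these lines.

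- **Trigger.** A study-level halt follows (a) any SAE not yet judged unrelated on the five-level scale; (b) any AE judged possibly, probably or causally related to the LiveOCT device or its procedures that raises a safety concern in the CI's assessment, including any laser-related eye event; or (c) a device deficiency with potential for serious harm.
- **No halt.** Unrelated non-serious AEs are recorded, graded and assessed for causality while the study continues.
- **Restart.** The sponsor, with the steering committee, reviews each halt and documents the restart once the event is judged unrelated or the risk is mitigated. Otherwise section 11 applies.
- **Links.** Keep the participant-level testing stop, cross-refer sections 11 and 16.2, and state that the five-level scale, now set out for SAEs, is used for all AEs so that (b) can be applied.

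The cost is an amendment of a few sentences, with no extra patients or data. The downside is that unrelated or trivial non-serious events no longer halt the study automatically, so more rests on the CI's prompt assessment of relatedness and safety concern.
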